**Figure 3. Study location – The Ilahita/Albinama/Wosera area, East Sepik Province, Papua New Guinea**

## 5.2 Inclusion/Exclusion Criteria

Children are eligible for participation in this study if they fulfill the following criteria:

- aged 5-10 years ( $\pm 3$  months in children without known date of birth),

- permanent residents of the area,
- absence of history of hypersensitivity reactions to the pre-treatment drugs.

At enrollment and upon informed consent, all eligible participants (see Section 5.1 above for criteria) will be screened for the following exclusion criteria:

- chronic illness,
- severe malnutrition (weight-for-age nutritional Z score [WAZ] <60th percentile)
- severe anemia (Hb <5 g/dL),
- G-6-PD deficiency (<60% G-6-PD activity)
- permanent disability, which prevents or impedes study participation.

Any 1 or more of the criteria is sufficient to exclude study participation.

Children with moderate to severe anemia (i.e. Hb 5 - 8 g/dL) can be enrolled, but will be treated according to national guidelines with a full course of antimalarials, albendazole and 4 weeks of daily oral iron supplementation. Children with severe malnutrition and severe anaemia (Hb < 5.0g/dL) will be referred to the local health centre for treatment according to national treatment guidelines.

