## 4 STUDY DESIGN

In this study 500-600 children aged 5-10 years will be screened, enrolled and randomized to 2 arms of a longitudinal cohort study. The randomized arms will comprise:

- 250-300 children pre-treated with 3 days Chloroquine (CQ), 4 weeks Primaquine (PQ) and 3 days Coartem (CO)
- 250-300 children pre-treated with 3 days Chloroquine (CQ), 4 weeks Placebo (PL) and 3 days Coartem (CO)

At enrolment all eligible children aged 5-10 years in the study area will be screened for Glucose-6-Phosphate Dehydrogenase deficiency (G-6-PD) and the presence of severe anaemia or malnutrition. Children with less than 60% G-6-PD activity, haemoglobin <5g/dl or severe malnutrition (weight-for-age nutritional Z score [WAZ] <60th percentile) will be excluded from the study. All other children will be randomized to the two treatment arms of the study.

Drug treatment will commence at enrolment. All children will receive CQ on days 1-3. Children will also receive either PQ (0.5 mg/kg) or placebo on days 1-5, 8-12, 15-19 and 22-26 (i.e. Monday to Friday for 4 weeks). During the third week of drug treatment all children will receive CO on days 15-17 (according to national treatment guidelines). Children will be actively monitored for side effects including measurement of haemoglobin levels at days 1, 8, 15 and 22.

Following completion of treatment, children will undergo a clinical examination and a 10 mL venous blood sample will be collected on day 29 (i.e. 26 days after their last dose of CQ, 12 days after their last dose of CO and 3 days after their last dose of PQ or PL).

Subsequently, all enrolled children will be followed using 2-weekly active and continuous passive case detection at a local health centre for 8 months (Week 2-32). Active follow-up consists of morbidity surveillance visits to monitor clinical malaria illness not reported to a health facility, as well as blood sampling for the detection of asymptomatic malaria. These visits will include collection of a medical history of the preceding 2 weeks to determine incidence of malarial infections and bed net usage, a physical examination, measurement of axillary temperature. A 250µl finger prick blood sample will be collected every 2 weeks for the first 12 weeks and 4 weekly thereafter, i.e. weeks 2, 4, 6, 8, 10, 12, 16, 20, 24, 28 and 32.

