**Table 2. Checklist for Assessment of Participant Health Status**

| Measurement or Health Indicator       |                                                                                                          |                       |
|----------------------------------------------|----------------------------------------------------------------------------------------------------------|-----------------------|
| Growth Measurements                          | Weight for age                                                                                           | Below 60th percentile |
| Axillary Temperature                         |                                                                                                          | ≥37.5°C               |
| Symptoms of Illness                   |                                                                                                          |                       |
| Fingers (previous blood draw puncture sites) | Redness, irritation, pus, swelling                                                                       |                       |
| Present Clinical Symptoms of Illness         | Chills
Sweating
Cough
Diarrhea
Convulsions                                                   |                       |
| Reported Symptoms of Illness                 | Fever
Chills
Sweating
Headache
Earache
Cough
Diarrhea
Abdominal Pain
Convulsions |                       |

The parents and/or guardians of the participant will be informed if their child's growth measurements and temperature are indicative of a health risk. If at the time of the study visit, the child is ill, has any of the signs or symptoms listed above, has measurements indicating that the child may be malnourished or is at risk of malnutrition, or may require clinical attention, the Nursing Officer will initiate treatment locally or recommend transfer to Albinama health center or Maprik Hospital. At the end of Study Team Visits, the field study team will provide transportation for ill study participants to the Albinama health center at no cost.

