## **7.2 Enrolment/Prescreening & Randomisation**

Upon presentation at the enrollment/screening visit, the PNGIMR study team will confirm the eligibility of participants (see Section 5.2 above for eligibility and exclusion criteria) and administer written informed consent (see Section 14.3 for details of consent procedures).

In the event an eligible child is excluded from the study, the PNGIMR field study team will record the reason for exclusion in the study log book. Children diagnosed with severe malnutrition or severe anemia will be referred to nearest health center or (conditional on parental or guardian consent) admitted to the nearest hospital for treatment. All children will receive (preventative) treatment for anaemia unless medically contraindicated.

All children that have normal G-6-PD activity will be randomized to the different treatment groups

Details of the procedures of enrollment/prescreening visit and randomization are given in Section 6.1.

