### **7.6 Criteria for Discontinuation or Withdrawal of a Subject**

Parents and/or guardians may withdraw their child at any time from the participations in this study.

A participating child will be discontinued from the study if 1 of the following criteria are fulfilled:

- the participant moves away from the selected study villages for a period longer than 2 months
- the participant develops a chronic illness that impedes continuation in study. Children developing severe anemia (Hb <5 g/dL) or severe malnutrition (WAZ <60%) may be discontinued by the study physician if medically indicated.

Participants who are discontinued because of acute or chronic illness may continue to consult the study team nurses during 2 weekly morbidity visits for health problems, if they wish to do so.

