### **15.5 Protocol Deviations**

The protocol will be adhered to for the entire duration of the study. In particular, no deviations from enrollment and exclusion criteria are permitted.

Adherence to protocol will be monitored by the study coordinator. In addition, protocol violations (eg, exclusion criteria) will be assessed regularly as part of the QC/QA procedures.

Should protocol deviations occur, the study supervisor will inform the principal investigator of the time and nature of the deviations. The PI will then inform the IRBs and if required, amendments to the protocol will be sought.

A protocol deviation is any noncompliance with the clinical trial protocol, GCP, or Manual of Procedures requirements. The noncompliance may either be on the part of the subject, the investigator(s), or the study staff. As a result of deviations, corrective actions should be developed by the site and implemented properly.

It is the responsibility of the site to use continuous vigilance to identify and report deviations within 5 working days to the study coordinators, who will maintain a log of protocol deviation log. All deviations from the protocol must be addressed in the subject's CRF. The study coordinator will take the necessary steps to prevent re-occurrence of similar deviations.

.

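### The severe-malnutrition exclusion is set at the 60th percentile of weight-for-age (Sections 4 and 5.2) and at 60% in Section 7.6; the first cannot mean severe, the second is not a Z value, and no growth reference is named

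*Protocol*

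**What the plan says.** The cut-off for low weight appears in four places in the protocol.

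- Section 5.2 lists as an exclusion criterion "severe malnutrition (weight-for-age nutritional Z score [WAZ] <60th percentile".
- Section 4 has the same wording: children with "severe malnutrition (weight-for-age nutritional Z score [WAZ] <60th percentile) will be excluded from the study".
- Section 7.6, on discontinuation, expresses the same condition differently: children developing "severe malnutrition (WAZ <60%) may be discontinued by the study physician" if medically indicated.
- Table 2 in Section 6.1.8, the checklist used at study visits, has an entry for weight for age: "Below 60th percentile". It mentions neither a Z score nor severe malnutrition.

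Other sections give the criterion its force. Section 5.2 states that "Any 1 or more of the criteria is sufficient to exclude study participation". Section 15.5 states that "no deviations from enrollment and exclusion criteria are permitted" and that "protocol violations (eg, exclusion criteria) will be assessed regularly as part of the QC/QA procedures". Section 7.2 attaches an action to the label: "Children diagnosed with severe malnutrition or severe anemia will be referred to nearest health center". Section 2.3.1, discussing the risk of frequent blood sampling, says that severely malnourished children will not take part.

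Section 6.1.2 records age, sex and weight at screening. No section names the growth reference against which weight is to be judged.

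**The concern.** A Z score counts standard deviations from a reference median. A percentile can be converted to a Z score, but the 60th percentile lies on the heavy side of the median, so a child of exactly average weight would meet the definition of severe malnutrition. The figure in Section 7.6 is a bare percentage attached to a Z score, and the protocol does not say what it is a percentage of.

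The consequence is practical. Staff who follow the text exclude ordinary children. Staff who use a sensible cut-off are applying one that the protocol does not contain, although it allows no departure from its exclusion criteria and promises to audit them. The same undefined label decides who is referred for treatment, and it is part of the reassurance given about blood sampling.

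**Working it through.** The protocol gives no figure to reproduce here, so the check is to work out what each wording would mean. The cut-offs come from Sections 4, 5.2 and 7.6, and the planned enrolment of 500 to 600 from Sections 4 and 5.1. The protocol gives no weight distribution. I therefore assume a coefficient of variation (CV) of weight at a given age and sex of 12% to 16%, and try both a normal and a lognormal model (log-scale SD taken as the CV).

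**1. The percentile read literally.** Φ⁻¹(0.60) = +0.253. By definition 60% of a reference population lies below it. In weight terms, under the normal model, this is 1 + 0.253 × CV, or 1.030 to 1.041 times the median (CV 12% to 16%). Enrolling 500 children from a reference-like population would require screening 500 / (1 − 0.60) = 1,250. If local children were on average one SD below the reference (an assumption), the share excluded would be Φ(0.253 + 1) = 0.895, about 89%.

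**2. The percentage read as percent of the reference median.** This reading is an inference.

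- Normal: Z = (0.60 − 1) / CV
- Lognormal: Z = ln(0.60) / CV = −0.511 / CV

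| CV | Z, normal | Share below | Z, lognormal | Share below |
|---|---|---|---|---|
| 12% | −3.33 | 0.04% | −4.26 | 0.001% |
| 14% | −2.86 | 0.21% | −3.65 | 0.01% |
| 16% | −2.50 | 0.62% | −3.19 | 0.07% |

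The range is therefore 0.001% to 0.6% of a reference population. Among 500 to 600 reference-like children, the normal model gives 0.2 (500 × 0.0004) to 3.7 (600 × 0.0062). The lognormal model gives at most 600 × 0.0007 = 0.4.

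**3. A conventional Z cut-off for comparison.** Φ(−3) = 0.00135, so WAZ below −3 takes in 0.13% of a reference population. As a share of the median:

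- Normal: 1 − 3 × CV = 64% down to 52%
- Lognormal: exp(−3 × CV) = 70% down to 62%

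Under the normal model this range straddles 60% of the median; under the lognormal model it lies wholly above it. The two candidate definitions are neighbours, but they are not interchangeable.

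**4. Side by side.** One label, severe malnutrition, covers about 60% of a reference population on the literal percentile and well under 1% on the likely intent. No plausible choice of CV or model closes that gap.

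**The case against.** The strongest reply is that nobody will be misled. Section 6.1.1 puts screening in the hands of registered nurses supervised by a specialist physician, Section 13 leaves field tasks to SOPs, and a growth-reference table is ordinary SOP content. No outcome, risk-time rule or analysis uses the threshold; nutritional state appears in Section 11.3.1 only as a possible covariate. On the likely intent only a handful of children are involved, if any. Most of this stands, and it is why the point is minor. It does not make the text right: an SOP with a workable cut-off would contradict the written criterion that Section 15.5 requires to be followed.

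It is also fair to say that Table 2 is a list the nursing officer considers alongside signs and symptoms. It is not an eligibility rule, and an over-inclusive prompt does not miss thin children. That stands too. The entry still flags children of average weight, so it does little to pick out those who may be malnourished.

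Three stronger readings are tempting, and the documents support none of them.

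- *The trial would lose 60% of its candidates.* That is what the words say, not what to expect; staff would very probably not apply the rule literally.
- *Sections 5.2 and 7.6 set two different thresholds on two known scales.* Section 7.6 may be shorthand for the Section 5.2 wording. Reading it as percent of median is plausible, but no section says so.
- *The results are compromised.* The exclusion is applied at screening, before randomisation, so it falls on both arms alike, and discontinuation under Section 7.6 is at the physician's discretion.

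**Conclusion.** The defect is real and minor. The exclusion threshold in Sections 4 and 5.2 is wrong as written, because Z = +0.25 cannot define severe malnutrition. Section 7.6 states the same condition in a form that is not a Z value, and without a named growth reference the intended cut-off cannot be recovered with certainty.

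The conversion of the 60th percentile needs no assumption. The small share under the likely intent rests on the assumed CVs, on the choice of normal or lognormal model, and on treating local children as reference-like. Its exact value is therefore soft, but its order of magnitude is enough to show that the two readings are far apart. What is affected is who is eligible, who is referred, whether the criterion can be audited, and how the enrolled population can be described.

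**What to change.** Before screening, put one definition in Sections 4, 5.2 and 7.6. Two forms would serve:

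- weight-for-age below 60% of the median of a named growth reference covering ages 5-10, which is probably what was meant; or
- WAZ below −3 SD on that same reference, with a note that this cut-off is not identical to 60% of the median.

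In Table 2, replace the 60th-percentile entry with a valid low-weight flag on the same reference. The study physician should choose its level, since the checklist also looks for children at risk and the protocol does not indicate a value.

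The cost is a wording correction in three sections and one small clinical decision for Table 2. Age, sex and weight are already recorded at screening, so no new measurement is needed, and design, sample size and analysis stay as they are.

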## **6 STUDY PROCEDURES/EVALUATIONS**

### **6.1 Study Procedures**

An overview of the study procedures is provided below and is discussed in greater detail in the following subsections.

#### **6.1.1 Field Study Team**

The study will be coordinated and day-to-day activities will be carried out by 2 PNGIMR field study teams with qualified registered nurses. All study staff are trained specifically to conduct informed consent, recruit participants, and organize and conduct the collection of blood and other measurements based on the research collaborators' study protocols. The study coordinator has received appropriate human subjects protections and study conduct training to conduct the study according to Good Clinical Practice (GCP) guidelines. The team will be supervised by a study coordinator and Specialist Physician on and off site. All clinical staff have the necessary registration with PNG nursing and medical boards and are thus allowed to dispense drug treatments.

#### **6.1.2 Enrollment and Screening**

Community awareness will be carried out through community leaders, village elders, health authorities, and village Reporters in the study area. An Information session for the parents of participating children will then be organized in the villages in the form of meetings to brief them on the broad aims and objectives of the study. After these meetings, a census of eligible children in the study area will be carried out before a formal informed consent is obtained (see section 6.0) from the parents to enroll their children in the study.

Following these consultations prospective participants will be screened for their suitability for inclusion in the study. After obtaining informed consent from parents or legal guardians, children will be screened for eligibility and their demographic (age, sex) and anthropometric data (weight) recorded and Hb levels determined. In order to prevent treating children with G-6-PD deficiency with primaquine, all children will be tested for G-6-PD deficiency at time of enrollment. All eligible children will be assigned a unique PNGIMR identification number. This number will be used to identify that child for the duration of the study.

Children with reported symptomatic illness will be examined by the study team and treated as required. In children with presumptive malaria illness the illness will be diagnosed on the spot using a rapid malarial diagnostic test (RDT). Children with a positive RDT test and/or and Hb < 8 g/dL will be treated with a full course of Coartem in addition to the albendazole and oral iron supplementation.

### **6.1.3 Randomisation**

Only children with normal G-6-PD status (>60% G-6-PD activity) will be randomised to the 2 study arms, i.e. CQ/PQ/Coartem, CQ/PL/Coartem. Every child's health (record) booklet will be clearly marked with a study identifier and study identification number. For children without or with a badly damaged health book, new health books will be issued at no cost to the participant. At any study contact, the study team will record all medically relevant data collected during their examination of the child.

### **6.1.4 Drug Treatment**

Drug treatment will at enrolment. All children will receive a course of course of Directly Observed Treatment (DOT) with CQ on days 1-3. Depending on the treatment arm children have been randomized to, they will also receive DOT of either PQ (0.5 mg/kg) or placebo(PL) on days 1-5, 8-12, 15-19 and 22-26 (i.e. Monday to Friday for 4 weeks). The use of placebo (PL) allows both the participants and study teams to be blinded to the treatments arms. During the third week of drug treatment all children will receive Coartem on days 15-17. All drug treatments will be given with food and observed by the study team. If children do not swallow the drugs properly or vomit them within 30 minutes of administration another dose will be administered.

In order for all children to complete treatment at the same time, the following schedule will be implemented for both rounds of drug treatment:

- Week 1: Commence CQ/PQ and CQ/PL treatment regime
- Week 2: Continue PQ and PL treatment regime
- Week 3: Commence Coartem/PQ and Coartem/PL treatment regime
- Week 4: Continue PQ and PL treatment regime

Treatment side effects will be monitored by study staff at DOT treatment time points. Hemoglobin will be measured at regular intervals during the treatment period to assure that no children are undergoing a hemolytic reaction to primaquine. Children that show adverse reactions to chloroquine, primaquine or Coartem will be excluded from further pre-treatment and subsequent participation in the study. Parents and/or guardians of study participants will be encouraged to seek

medical care for their children, to report any symptoms of malaria, fever, or illness at the earliest opportunity, and to report any anti-malarial treatments received or used. Parents and/or guardians of study participants will be encouraged to seek medical attention immediately if their child has any sign or symptoms of illness or any other condition that they deem as a threat to their child's well-being. They will be advised of their rights to withdraw from the study at anytime should they wish to do so and no medical care or treatment will be refused by the PNGIMR field staff as a form of penalty.

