### **6.1.5 Baseline measurements and sample collection**

Baseline measurements and venous blood collection (10 mL) will be conducted 4 weeks after enrollment and 3 days after the final dose of the PQ and PL drug regime. During the baseline visits the PNGIMR field study team will conduct the following tasks:

- Assess the child's health status including
  - body temperature
  - symptoms of malaria or other infections
  - spleen size
- Interview the parent and/or guardian and record:
  - history of child's bed net use in 2 weeks prior,
  - child's history of febrile illness/malaria in 2 weeks prior,
  - child's history of malaria treatment in 2 weeks prior (except treatments given by study),
- Check the child's health records booklet for recent health center visits and record applicable information,
- Collect 10 mL venous blood sample,
  - Prepare thin and thick blood smears,
  - Prepare filter paper blood spot
  - Archive samples for laboratory analyses (PCR-typing plus auxiliary immunology),

If the participant has symptoms of clinical malaria he/she will be diagnosed in the field using a rapid diagnostic test (RDT) for malaria and HemoCue® for Hb concentration. For children excluded from undertaking RDT tests, blood smears will be read overnight for malaria diagnosis. Upon positive RDT, or positive blood smear or in the case of moderate-to-severe anemia (Hb <8.0 g/dL) the study team will initiate treatment with Coartem according to national treatment guidelines.

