## **9 SAFETY ASSESSMENT AND REPORTING**

This study will treat all children with common anti-malarials with well known safety profiles. Although generally well tolerated in non-G-6-PD deficient children, treatment with primaquine may be associated with mild side effects. The study will therefore actively monitor children for side effects during treatment

As described previously, the PNGIMR has conducted an earlier cohort study in the same population that included careful monitoring of adverse events. Based on our experience from that study, while SAEs occurred regularly none of them were study-related adverse experiences, as defined below..

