### **9.3.2 Type and Duration of the Follow-up of Subjects after Adverse Events**

All SAEs/AEs will be followed until satisfactory resolution or until the Study Clinician deems the event to be chronic or the patient to be stable.

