#### 11.1.2 Primary Outcome Measures

##### **11.1.2.1 Incidence of clinical *P. falciparum* or *P. vivax* episodes during the 32 weeks of follow-up**

The comparison of the incidence of clinical *P. falciparum* and *P. vivax* episodes between the 2 study arms is a primary objective of the study and will be evaluated by assessing differences in both the incidence of *P. falciparum* *P. vivax* episodes over 32 weeks of follow-up and the incidence of first or only *P. falciparum* / *P. vivax* episodes

Children will be considered 'at risk' until they reached the endpoint of interest, withdrew, were lost to follow-up or completed the study. For clinical and molecular endpoints children were censored on the last day before the first of two consecutively missed active follow-up visits

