## **11.2 Sample Size Considerations**

### **11.2.1 Primary Outcome Measures**

No estimates for time to first *P. vivax* infection are available for the study community however, in the above-mentioned treatment time-to-reinfection study in children 6-12 years of age in neighbouring Madang province the median time re-infection was 54 and 118 days for PCR and light microscopically detected *P. vivax* infections, respectively. Assuming a 50% decrease in time to first new *P. vivax* infections following LLIN distribution then a sample size of 200 children per arm be sufficient to find a reduction of 30% (hazard ratio 0.70) and 34% (hazard ratio 0.66) of PCR and LM-detectable *P. vivax* infections in the CQ/PQ/CO compared to the CQ/PL/CO group with a power of 90%. This sample size was increase by 25% to account for loss of follow-up and by 5% for children that receive less than 14 days of directly observed primaquine treatment/

In a recently completed cohort study in this region, the incidence of clinical *P. falciparum* malaria in children aged 1-3 years was estimated at 2.6 episodes per child per year (any density). Although no estimates for the incidence of clinical *P. falciparum* malaria in children aged 5-10 years in this region, in a recent treatment time-to-reinfection study in children 6-12 years of age in neighbouring Madang province, the incidence was estimated at 1.7 episodes per child per year (any density). The recent distribution of long-lasting insecticide treated bednet (LLIN) will have reduced this incidence by 60%.

Thus, assuming an incidence of 0.5 episode of *P. falciparum* per child per year (any density in this cohort of similarly aged children, a sample size of 500 children will thus be sufficient to detect 20% decrease in incidence between the two treatment arms with a power of 90%.

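### Protocol 6.1.4 ends study participation, not only study drug, for randomised children who react to treatment, so their outcomes are lost and the loss can differ by arm

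*Protocol*

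**What the plan says.** Protocol 6.1.4 (Drug Treatment): "Children that show adverse reactions to chloroquine, primaquine or Coartem will be excluded from further pre-treatment and subsequent participation in the study". The sentence does two things. It stops study drug, and it ends the child's time in the study. No severity threshold is attached.

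The surrounding text fixes when and in whom this happens:

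- **Arms.** All children receive chloroquine and Coartem; one arm receives primaquine and the other placebo (section 4). On blinding, 6.1.4 says: "The use of placebo (PL) allows both the participants and study teams to be blinded to the treatments arms".
- **Expected reactions.** Section 9 says that "treatment with primaquine may be associated with mild side effects" even in children who are not G-6-PD deficient. No rate is given.
- **Start of outcome observation.** The baseline visit takes place "3 days after the final dose of the PQ and PL drug regime" (6.1.5), and active follow-up runs over weeks 2-32.
- **Risk time.** "Children will be considered 'at risk' until they reached the endpoint of interest, withdrew, were lost to follow-up or completed the study" (11.1.2.1). Children excluded for a reaction are not mentioned.
- **Discontinuation.** 7.6 opens with "A participating child will be discontinued from the study if 1 of the following criteria are fulfilled" and lists moving away and chronic illness, with severe anaemia or malnutrition left to the study physician. An adverse drug reaction is not listed.
- **Adverse events.** 9.3.2: "All SAEs/AEs will be followed until satisfactory resolution or until the Study Clinician deems the event to be chronic", or the child is judged stable.

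**The concern.** Stopping a drug and stopping observation are separate decisions. The first is clinical and is not questioned here. The second determines whether the randomised groups can be compared as randomised.

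Because the rule acts between randomisation and baseline, a child removed under it has no follow-up time at all. The arms differ only in primaquine versus placebo, so a reaction to primaquine can remove a child in one arm whose counterpart in the other arm stays. Blinding does not prevent this, since the trigger is the reaction and not knowledge of the arm. If children who react also differ in infection risk, what remains is a comparison of children who tolerated primaquine with children who tolerated placebo. The first aim of the trial is exactly this randomised contrast.

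An analysis plan can define an all-randomised population, but it cannot supply outcomes that the protocol has stopped collecting. The point therefore belongs in the protocol and has to be settled before enrolment.

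**Working it through.** **Timing.** Drug runs from day 1 to day 26 and baseline is day 29 (section 4). A reaction during treatment therefore removes the child before any outcome visit.

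**The plan's own figure.** The protocol gives no figure for this rule, so there is none to reproduce. As background, the *P. vivax* sample size in 11.2.1 (200 per arm, hazard ratio 0.70, 90% power) can be checked at the stated PCR median of 54 days, with exponential times, 224 days (32 weeks) and two-sided alpha 0.05. Alpha is an assumption, as the protocol does not state it.

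- Infection risks: 1 - exp(-ln2/54 × 224) = 0.944 on placebo; with hazard × 0.70, 0.866.
- Events: 200 × 0.944 + 200 × 0.866 = 362.
- Power (Schoenfeld): Φ(√362/2 × |ln 0.70| - 1.96) = Φ(1.43) = 0.924, in line with the stated 90%.

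**Bias model.** Inputs that are assumptions:

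- q = share of the primaquine arm removed: 2%, 5% or 10%. Of 250 children that is 5, 12.5 or 25.
- k = infection hazard of removed children relative to the others: 0.5 or 2.
- The same kind of child stays in the placebo arm, so removal is wholly one-sided.
- Baseline median 54 or 108 days, because the 50% decrease in 11.2.1 can be read in more than one way.

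With b = ln2/median and F(h) = 1 - exp(-224h), a group with hazard h contributes F(h) events and F(h)/h days per child.

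- Placebo rate = [(1-q)F(b) + qF(kb)] / [(1-q)F(b)/b + qF(kb)/(kb)].
- Primaquine rate after removal = 0.70 × b.
- The first-infection rate ratio is the second divided by the first.

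Example 1: median 54, q = 5%, k = 0.5, so b = 0.012836.

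- Events: 0.95 × 0.9436 + 0.05 × 0.7625 = 0.9345.
- Days: 0.95 × 73.51 + 0.05 × 118.81 = 75.78.
- Placebo rate: 0.012333. Ratio: 0.70 × 0.012836 / 0.012333 = 0.729.

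Example 2: median 108, q = 5%, k = 2, so b = 0.006418.

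- Events: 0.95 × 0.7625 + 0.05 × 0.9436 = 0.7716.
- Days: 0.95 × 118.81 + 0.05 × 73.51 = 116.54.
- Placebo rate: 0.006620. Ratio: 0.70 × 0.006418 / 0.006620 = 0.679.

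Range over both medians and both values of k:

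| Removed from primaquine arm | Estimate when there is no effect | Estimate when true ratio is 0.70 |
|---|---|---|
| 2% | 0.99-1.02 | 0.69-0.71 |
| 5% | 0.97-1.04 | 0.68-0.73 |
| 10% | 0.94-1.08 | 0.66-0.76 |

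With everyone retained, the same model gives 1.00 under no effect and 0.70-0.71 under a true ratio of 0.70. If the 50% decrease is read literally as halved times (median 27 days), the 10% row for a true ratio of 0.70 becomes 0.67-0.77, so the conclusion does not depend on that reading.

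**Power.** Removing 10% of the primaquine arm leaves 180 children there. At 54 days, power falls from 0.924 to 0.911; at 108 days, from 0.846 to 0.829. The issue is bias, not sample size.

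**The case against.** Several stronger readings are tempting, and the protocol does not support them.

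- **That primaquine safety data are thrown away.** They are not. Side effects are checked at each observed dose (6.1.4), haemoglobin is measured on days 1, 8, 15 and 22 (section 4), the date and reason of termination are recorded (7.5), study-related events are reported (9.1, 9.3) and events are followed to resolution or stability (9.3.2). What goes is the scheduled day-29 examination and the fortnightly follow-up of the children who reacted.
- **That the randomised comparison is broken.** Bias needs removal that both differs by arm and relates to infection risk. Chloroquine and Coartem are shared, so some removals fall in both arms alike, and 2.3.1 reports good tolerability of primaquine in 150 younger children. Numbers may be small.
- **That every mild side effect ends participation.** 6.1.4 itself re-doses a child who vomits within 30 minutes. The threshold is undefined; it is not stated to be zero.
- **That there is a second, primaquine-only exclusion.** 11.2.1 enlarges the sample "by 5% for children that receive less than 14 days of directly observed primaquine treatment". That is an allowance for incomplete dosing and is compatible with keeping those children in their arm. No analysis section excludes them.
- **That 6.1.4 flatly contradicts 7.6 and 9.3.2.** The list in 7.6 is not declared exhaustive, and an event can be followed to resolution in a child who has left the outcome cohort. These are gaps to reconcile: 7.6 omits the rule, and no route is given for event follow-up after removal, since 7.5 provides no termination visit.
- **That a worst-case bound on risk shows a large share of the planned difference at stake.** With 5% removed, the primaquine-arm risk could lie between 0.95 × 0.634 = 0.602 and 0.602 + 0.05 = 0.652, against a difference of 0.763 - 0.634 = 0.129. But the trial is sized on hazard ratios. Those risks require a 108-day median that the protocol does not state, and the lower bound supposes that no removed child would ever be infected.

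All of these objections stand. None of them reaches the core point: the clause stops outcome collection in randomised children for a reason that can depend on the arm.

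**Conclusion.** The concern holds as a design weakness with potential for bias. Under one-sided removal, a true hazard ratio of 0.70 would be estimated at about 0.69-0.71, 0.68-0.73 or 0.66-0.76 with 2%, 5% or 10% of the primaquine arm removed. The error can go either way: upwards if the children who react are at lower infection risk, downwards if at higher. At low reaction rates it is slight.

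These figures rest on assumed removal rates and relative hazards, exponential times and removal confined to one arm. The protocol supplies no reaction rate against which to narrow the range. If removal were equal in both arms, or unrelated to infection risk, there would be no bias, but with outcomes uncollected the second condition could not be verified from the trial's data. The case for acting rests on that irrecoverable loss and on how little the change costs, not on a large expected error.

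**What to change.** In Protocol 6.1.4, leave the decision to stop study drug as it stands and delete the clause that ends participation in the study. State that these children remain in outcome and safety follow-up where consent and the study physician allow. Which procedures suit a child who has reacted, including the venous sample, stays with the physician.

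In 11.3, state that all randomised children with follow-up are analysed in their assigned arm.

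Reconcile 6.1.4, 7.6 and 9.3.2, so that one place says when a child leaves drug, when a child leaves the study, and how adverse events are followed in each case.

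The cost is a few sentences and a few extra visits by teams already at the schools every two weeks. Children who stopped primaquine early will dilute the estimated effect slightly. The change has to be made before enrolment to be of use.
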